## 2. Objectives

### 2.1. General objective

To assess the effectiveness of newly developed supplementary iCSBs and LNS for the management of children 6-23 months old with moderate acute malnutrition in Burkina Faso, by determining their effects on accrual of lean body mass, linear growth, functional and biological outcomes.

### 2.2. Specific research objectives

#### *Primary objective:*

- To assess the effectiveness of a 3 month supplementation with newly developed iCSBs and LNS on the increase of lean body mass among children 6-23 months old with MAM in Burkina Faso.

#### *Secondary objectives:*

- To assess the effectiveness of a 3 month supplementation with newly developed iCSBs and LNS on weight-for-height increase, increase in MUAC, linear growth, thymic size, physical activity, child motor and language development, serum APPs, serum IGF-1, ferritin and hemoglobin, whole EFA blood concentrations and reported morbidity among children 6-23 months old with MAM in Burkina Faso.
- To compare the effectiveness of different soy qualities (dehulled soy versus soy isolate) and different amounts of protein provided by dry skimmed milk (DSM) on the outcomes among 6-23 months old children with MAM in Burkina Faso.
- To explore childcare practices related to supplementary feeding as well as the adherence to and acceptability of the food supplements.

#### *Other secondary objectives:*

- To suggest the most effective food and duration of supplementation for MAM management, according to age and nutritional status,
- To assess the level of baseline body composition, biological profile, physical activity and motor and language development of children 6-23 months old with MAM in Burkina Faso,

---

 By merging, in the LNS and the iCSBS arms separately, the dehulled soy groups and soy isolate groups on the one hand and the 0% DSM, 20% DSM and 50% DSM groups on the other hand.

- To identify anthropometric and other simple predictors of lean body mass,
- To compare the costs of the food products

### 3. Methods

#### 3.1. Effectiveness randomized controlled trial

##### 3.1.1. Study setting and study period

The trial will be conducted in selected district health centers “Centre de Santé et de Promotion Sociale” (CSPS) supported by ALIMA in the province of Passoré in the northern region of Burkina Faso. ALIMA’s program consists of support to district health structures for the management of severe acute malnutrition (SAM) in the District hospital of Yako and 53 CSPS in the province of Passoré. The trial will take place in five selected CSPS. Admission and follow-up take place 5 days a week on each site. The recruitment of children for the trial is expected to begin in August 2013. The intervention is planned for three months, with an additional three months of follow-up.

The prevalence of HIV among adults in Burkina Faso is 1.2 %. The estimated number of HIV infected children among our study participants is therefore likely to be very low.

##### 3.1.2. Study population

Children will be eligible for inclusion if they fulfill the following criteria:

- weight-for-height z-score (WHZ)  $\geq -3$  and  $< -2$  (based on the WHO growth standard) or
- MUAC  $\geq 115$ mm and  $< 125$  mm
- 6 to 23 months of age,
- resident in the catchment area at the time of inclusion,
- whose parents/guardians have signed (or thumb-printed whenever illiterate) the informed consent.

---

 From 7.30am to 4 pm, all year long.

 UNAIDS 2009

 According to the workload, prior MUAC screening might be implemented.

 A local calendar of events will be piloted. If it does not appear suitable for inclusion based on age, children would be included based on a combination of event calendar and height.

Will be excluded:

- Children with severe acute malnutrition defined as a WHZ < -3, and/or a MUAC <115 mm, and/or bilateral pitting oedema. They will be referred to the health centres or Yako hospital for appropriate treatment,
- Children with medical complications requiring hospitalization,
- Children whose household plans to leave the catchment area in the next 6 months.
- Children with a hemoglobin concentration <4g/dl or with evidence of a decompensate anemia (eg, dyspnea, tachycardia...). These children will be transferred to the ITFC supported by ALIMA for appropriate treatment.
- Children who have been treated for SAM or who have been hospitalized in the last 2 months,
- Children with known allergy to milk, peanut, CSB and/or RUTF,
- Children with a severe disability limiting the possibility of investigations,
- Children enrolled in any other nutritional program or part of any other study conducted in the area.

Children with MAM who do not wish to participate in the study or who are excluded due to some of the above mentioned criteria, will be referred to the national supplementary nutritional program currently supported by WFP.

Appropriate free care, including referral to nutritional rehabilitation or pediatric care at Yako hospital (supported by ALIMA) when needed, will be offered to children who are non-eligible due to SAM or decompensated anemia.

Children will be recruited among children presenting spontaneously at the CSPA. All children taken to CSPA will be screened for eligibility. Furthermore active case finding within the community by community health workers supervised by ALIMA will be done.

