### Participants

All children arriving spontaneously at the CSPS program sites will be screened for eligibility. Furthermore active screening will be done in the villages by community health workers supervised by ALIMA. Children will be eligible for inclusion if they fulfil the following criteria:

- 6-23 months of age
- weight-for-height z-score (WHZ)  $\geq -3$  and  $< -2$  (WHO growth standard) or
- MUAC  $\geq 115$ mm and  $< 125$  mm,
- resident in the catchment area at the time of inclusion,
- whose parents/guardians consented to participate.

Children suffering from or having received treatment for severe acute malnutrition (WHZ  $< -3$ , mid-upper-arm circumference  $< 115$  mm, oedema) in the last two months, children with medical complications requiring hospitalization or having been hospitalized in the last two months and children with known allergy to milk, peanut, CSB and/or RUTF will be excluded.

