# 1. Introduction

## 1.1. Background

Acute child malnutrition (wasting) is a major global health problem, resulting in considerable morbidity and mortality. Children surviving from malnutrition may grow up with impaired intellectual and working capacity (*Black RE et al, 2008*). It has been estimated that more than 19 million children worldwide suffer from severe acute malnutrition (SAM, defined by a weight-for-height  $< -3$  z-scores), and, in addition, more than 36 million (*Black RE et al, 2008*) from moderate acute malnutrition (MAM, defined by a weight-for-height between  $-3$  and  $-2$  z-scores), which may progress to SAM.

Research has advanced the treatment of SAM, and significantly reduced its case fatality due to improved management protocols (*Manary et al, 2008*) using special milk based formulas (F-75 and F-100) and lipid-based Ready to Use Therapeutic Foods (RUTFs). In contrast to SAM, the management of MAM has only recently started to get more attention. Children with MAM have typically been given fortified blended flours (FBF) made by mixing soy and maize flours with added vitamins and minerals, such as corn-soy blend (CSB). The impact of this approach has been regularly questioned over the last 30 years (*Beaton GH et al, 1982; Navarro-Colorado C, 2007*). Until recently, their apparent lack of impact has been attributed to programmatic factors, such as food sharing, or the effect of repeated infections limiting the impact of food supplementation. These limitations have been challenged by the success of treating and preventing MAM with RUTF in conditions where the same programmatic difficulties applied (*Defourny I et al, 2007; Isanaka S et al, 2009; Nackers F et al, 2010*).

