## 1.2. Investigational food supplements

Twelve investigational food supplements will be developed based on current available evidence (*[name] KF et al, 2009; Golden M, 2008*) and international guidance (WFP, WHO, MSF, ALIMA). These include improved CSB based supplements (iCSBS) and LNS combining different soy qualities and different amounts of total protein provided by dry skimmed milk (DSM), as follows:

- 3 iCSBS based on dehulled soy, with either 0%, 20% or 50% of total proteins provided by DSM
- 3 iCSBS based on soy isolate, with either 0%, 20% or 50% of total proteins provided by DSM
- 3 LNS based on dehulled soy, with either 0%, 20% or 50% of total proteins provided by DSM
- 3 LNS based on soy isolate, with either 0%, 20% or 50% of total proteins provided by DSM

Thus a total of 12 products, 6 in the form of LNS and 6 in the form of CSB.

---

 0%, 20% and 50% of total protein provided by DSM corresponds to 0%, 8% and 20% of total weight.

Both types of product will comply with the WHO technical note “Supplementary foods for the management of moderate acute malnutrition in infants and children 6 – 59 months of age”(WHO 2012)

The products will not have the same nutrient density per 100g, but will provide the same total amount of protein and micronutrients per daily serve (130g of CSB or 92g of LNS).

The fatty acid profile will be similar in all twelve products and the same supplier for the main raw material, dehulled soya and soy isolate, will be used for both LNS and CSBs.

A vitamin and mineral premix will be designed for all products and will meet the quantities specified in the WHO technical note. Some adjustments will be necessary between products because e.g. dry skim milk in larger quantities will be a significant contributor of e.g. calcium, potassium and phosphorous, and because the concentration of certain vitamins decreases during the preparation of CSB. The aim is a uniform micronutrient composition across all products for final consumption.

For a detailed description of the composition of the products, please see annex 2.

LNS will be provided in individual packaging, ready for consumption with no need for preparation or cooking. All LNS individual packs will have similar packaging, whatever the type of soy or the milk content, and will only differ by a number.

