#### **Safety**

Adverse events (AE): Although we do not expect the foods to cause any harm, peanut, milk, and soy proteins can be allergenic. AE could include: digestive symptoms (diarrhea and/or vomiting), cutaneous symptoms (hives) and, respiratory symptoms (wheezing) within one hour after ingestion of the food. The first dose of the products will be taken under observation and anaphylactic kits will be available at each recruitment sites, where the study nurse will be trained in how to respond to any allergic reaction. All signs of possible allergic reaction will be recorded as part of the fortnightly morbidity assessment, and will be treated accordingly. Serious AE related to this study could include: angioedema, anaphylactic reaction, and death. All serious AE will be immediately communicated to the trial manager who will ensure that they are addressed in an appropriate and timely manner and reported to all study investigators and trial sites, according to Good Clinical Practice. The trial manager will be responsible for the medical management of all adverse events, and will ensure referral to the national health system if necessary, including follow-up.

---

 Definition of the ICH-GCP glossary: Adverse Event : Any untoward medical occurrence in a patient or clinical investigation subject administered a pharmaceutical product and which does not necessarily have a causal relationship with this treatment. An adverse event (AE) can therefore be any unfavorable and unintended sign (including an abnormal laboratory finding), symptom, or disease temporally associated with the use of a medicinal (investigational) product, whether or not related to the medicinal (investigational) product. Serious Adverse Event (SAE): Any untoward medical occurrence that at any dose: results in death, is life-threatening, Requires inpatient hospitalization or prolongation of existing hospitalization, results in persistent or significant disability/incapacity, or is a congenital anomaly/birth defect.

Furthermore the national ethical review board will be notified and will be asked to advise the investigators of future actions to be taken.

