### *3.1.8. Randomization, sequence generation, allocation and concealment*

Each of the twelve food products (six CSB and six LNS) will be randomly letter coded by GC Rieber Compact by the letters M, N, P, Q, R, S, T, U, V, X, Y, Z, ( "O" is omitted due to similarity with "Q"). Two identical documents (code documents) stating which product corresponds to which code is prepared and placed in sealed envelopes also by GC Rieber Compact. The code documents are kept in safety boxes, one at the MSF-DK office, and one at the Dept. of Nutrition, Sports and Exercise, University of Copenhagen. The code will first be revealed following the primary analysis.

Stratified, blocked randomization will be used to randomly allocate children to the twelve experimental foods. Stratification will be done by recruitment site (CSPA), ie, separate random sequences will be made, one to be used at each of the five sites. This will ensure that site, which may be strongly associated with the outcome and thus an important potential confounder, will be equally distributed between the intervention groups. Blocked randomisation will be used, with varying block size, to ensure that for each site, children will

be allocated evenly to the trial arms. The random sequences (RS) are made using [www.randomization.com](http://www.randomization.com).

Sealed envelopes will be labelled with the unique patient code and will contain the intervention allocated to the patient. The envelopes will be opened only after the completion of the screening and the final recruitment of the patient, ensuring concealment.

In case two or more siblings are presenting MAM, only one child per mother will be included in the trial (i.e. the first child diagnosed with MAM or, if several siblings are diagnosed on the same day, one of them will be selected by simple random sampling). The other siblings will however benefit from the same nutritional intervention as her/his brother/sister (whether it is, the iCSBs or LNS group). For these siblings, no specific assessments would be done except the routine medical evaluation and standard anthropometric measurements.

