### **Safety analysis**

Safety analyses will be performed among participants having been randomized. The number of adverse events and serious adverse events will be presented for each group. Proportion of participants presenting with AE or serious AE will be compared between groups. Description of adverse events will be given.

Statistical analysis will be performed using Stata software.

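### Soy is in all 12 products and is named as an allergen, but the allergy exclusions reach it only through CSB or RUTF; siblings given study food have no stated checks and no place in the safety analysis

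*Combined protocol and SAP*

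**What the plan says.** **Exclusions.** Section 3.1.2 excludes "Children with known allergy to milk, peanut, CSB and/or RUTF". The Participants part of the Summary matches it: "children with known allergy to milk, peanut, CSB and/or RUTF will be excluded". Milk and peanut are named as ingredients; CSB and RUTF are products. Soy does not appear by name.

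**Allergens.** The Safety part of section 3.1.5 states that "peanut, milk, and soy proteins can be allergenic" and gives angioedema, anaphylactic reaction and death as possible serious events. It also provides for an observed first dose, anaphylactic kits at the recruitment sites and a trained nurse. Section 4.3 repeats the supervised first dose.

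**Products.** Section 1.2 lists four families of three foods, for example "3 iCSBS based on dehulled soy, with either 0%, 20% or 50% of total proteins provided by DSM", and concludes: "Thus a total of 12 products, 6 in the form of LNS and 6 in the form of CSB". Each family is based on one of the two soy ingredients.

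**Siblings.** Section 3.1.8 enrols one child per mother where several have MAM, then adds: "The other siblings will however benefit from the same nutritional intervention as her/his brother/sister". For these siblings it foresees only the routine medical check and basic anthropometry.

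**Safety population.** The Safety analysis part of section 3.1.13 says: "Safety analyses will be performed among participants having been randomized".

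**The concern.** The protocol names three allergens. It screens for two of them by ingredient and for the third only by way of products. The third is the one that no allocation can avoid. A screener following section 3.1.2 literally has no prompt to ask about soy, and a caretaker who reports a soy reaction to some other food has not reported anything on the list.

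The sibling provision raises a different problem. Children outside the trial are knowingly given an investigational food, but the plan does not say which exclusions apply to them, whether anyone asks about allergy, or how a reaction would be recorded. Because siblings are not randomized, the safety analysis as defined has no place for what happens to them. Section 3.1.8 also leaves open whether a sibling gets the identical letter-coded product or merely the same type of food (iCSB or LNS). Unless the code is recorded, a reaction could not be traced to a product.

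At stake are a consistent allergy screen and complete safety information on the children given these foods. The randomized efficacy comparison is not affected.

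**Working it through.** **Planned numbers (section 3.1.7), reproduced first.** n per group = 16·s²/d² with d = 0.4 SD, so 16/0.16 = 100. Allowing for 25% loss: 100/0.75 = 133.3, rounded up to 134. Total: 12 × 134 = 1608. This agrees with the plan and is used below only as a denominator.

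**Which named allergens are in which products (section 1.2).** Product count: 2 food types × 2 soy types × 3 milk levels = 12.

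| Allergen named in 3.1.5 | Products containing it | Planned children | Named in the exclusion? |
|---|---|---|---|
| Soy | 12 of 12 | 12 × 134 = 1608 | No; only indirectly, through CSB or RUTF |
| Milk (DSM above 0%) | 2 × 2 × 2 = 8 of 12 | 8 × 134 = 1072 | Yes |
| Peanut | Not shown; composition is in annex 2, which is not in the text reviewed | Not known | Yes |

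**How far the CSB entry reaches.** The abbreviations list and section 1.1 identify CSB as corn-soy blend, a mix of soy and maize flours. A child known to react to CSB is therefore excluded. The RUTF entry may catch others, but the text reviewed does not state whether RUTF contains soy. What remains is a child with a known soy allergy that was not recorded as a reaction to CSB or RUTF. That child meets no allergy exclusion. Half the planned children (6 × 134 = 804) are allocated to LNS, which is also soy based.

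**Siblings, text against text.**
- Section 3.1.2 says that all children brought to a site are screened for eligibility. It does not make giving a sibling the food conditional on passing.
- Section 3.1.5 records signs of allergic reaction in the fortnightly morbidity assessment. Section 3.1.8 does not list that assessment for siblings.
- Section 3.1.13 defines the safety population by randomization, and siblings are not randomized.

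**How many siblings.** The documents give no figure. As an assumption only, suppose 1% to 10% of enrolled children have one such sibling:
- 1%: 0.01 × 1608 ≈ 16 children; 16/(1608 + 16) = 1.0% of all children given a study food.
- 10%: 0.10 × 1608 ≈ 161 children; 161/(1608 + 161) = 9.1%.

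The width of this range shows that the scale cannot be settled from the plan.

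**The case against.** Several points on the other side have force.

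**Soy is partly covered.** A reader might infer that the exclusions ignore soy altogether. They do not: CSB is a soy product, and section 1.5 says it is still recommended for MAM in Burkina Faso, so a reaction to it is a plausible way for a soy allergy to become known locally. This narrows the gap to soy allergies known from elsewhere.

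**Soy may not be the only allergen common to all arms.** Milk is ruled out by the four products with 0% DSM. Peanut cannot be judged without annex 2. The documents support calling soy an ingredient of every product, not the sole named allergen in every product.

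**Silence is not a waiver.** A reader might infer that siblings are exempt from the exclusions and that their reactions go unreported. No section says so. General screening at the sites, the routine medical check, and the instruction to communicate every serious event at once could all extend to siblings. The supportable statement is that their application to siblings is not stated.

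**Safeguards exist.** The observed first dose and the kits are described for the products generally, without restriction to randomized children. They reduce harm once exposure has happened. They do not replace screening, and they do not bring sibling events into the results.

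**The safety population is conventional.** Non-randomized siblings do not belong in a between-group comparison of adverse-event proportions. That is right, and it is why the remedy is a separate listing and not a wider analysis set.

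**Conclusion.** The point holds in a limited form. The exclusion lists and the safety section do not match: soy is named as an allergen and is in 12 of 12 products, but the exclusions reach it only through a known allergy to CSB or RUTF. A child with a known soy allergy not recorded in that way is eligible as written. Siblings receive study food with no stated eligibility or allergy check and no stated adverse-event recording, and they fall outside the safety analysis as defined.

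The likely size is small. The documents give no frequency of known soy allergy, and it is presumably rare at 6 to 23 months. The sibling count is unknown; 16 to 161 is an illustration resting wholly on the assumed 1% to 10%. If the age limit also applied to siblings, which the plan does not say, they would have to be twins or very closely spaced births, and the number could be low.

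This is an inconsistency and an omission that deserve correction because correction is cheap and concerns safety. It is not a flaw in the sample size, the power or the primary analysis.

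**What to change.** 1. Reconcile the allergy exclusions in the Summary and section 3.1.2 with the allergens named in section 3.1.5, so that the three places agree. Which criterion is clinically right is for the sponsor and investigators to decide.
2. Reconcile section 3.1.8 with sections 3.1.2 and 3.1.5. State which eligibility checks and which adverse-event recording apply to a sibling given a study product, and whether the sibling receives the same coded product. State that the product code is recorded.
3. Add to the Safety analysis part of section 3.1.13 a separate descriptive listing, by product, of reactions and serious adverse events in siblings. Keep it outside the randomized comparison, whose population stays as it is.

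The cost is a few sentences of text, a small addition to the sibling record and one extra listing. At screening, a negligible number of children would be affected.
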